### Blinding

Due to the nature of the intervention, it is impossible to blind the participants assigned to the study groups to the data collector. However, the outcome assessor will be blinded and instructed not to ask the participants whether or not they received the intervention.

### Data Management

Data will be collected in paper format. A file for each subject will be stored in numerical order in a secure place and manner. Files will be maintained at the recruitment center for 3 years after completion of the study. The statistical expert will prepare the data generated by the IBM/SPSS statistical software (version 16). This expert will train the data clerk to enter the data by specific codes and labels. Also, after finishing the data entry, all data will be double checked. All forms related to the study will be kept in a locked cabinet with restricted access in the recruitment center. All reports will be prepared in a manner in which no individual participants can be identified.

### Data Monitoring

Three researchers from TUMS not involved in the study and chosen by the university will monitor data and supervise the conduct of the study.

### Statistical Methods

Statisticians will prepare the data sheets to collected data. Data will be entered into the SPSS software (version 16). The Kolmogorov-Smirnov test will be used to normality. A transformation approach will be used to handle non-normal distribution. For the between-group comparison of continuous and categorical baseline characteristics, independent *t* test and chi-square test will be used. For categorical variables between the 2 groups, the two-tailed Fisher exact test will be used instead of the chi-square test in the case of too small expected cell frequencies. A *P* value <.05 will be considered statistically significant.

#### Primary Analysis

Baseline scores for each scale of SCHFI including self-care maintenance, management, and confidence will be compared in both groups by an independent *t* test. Due to the measurement of self-care behavior at baseline and at monthly time intervals, we will calculate the mean of monthly self-care scores in order to compare the mean of self-care behavior after the intervention in both groups. Also, because of the frequent measurement of self-care behavior, we will also use *P* value correction based on the Bonferroni method [58]. A linear logistic regression procedure will be applied to determine the factors affecting self-care behavior. The odds ratio will be reported with 95% CI.

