### Data Collection

Eligible patients will be asked to read and sign a written informed consent form. The research nurse will then collect demographic and clinical characteristics by participant self-reporting and from a medical chart and then record these in data collection forms (see Table 1). Also, participants will be asked to complete baseline surveys (SCHFI, HF knowledge, HFQOL, and health literacy) by themselves in the HF clinic before randomization.

In order to assess participant health literacy, we will use the Heart Failure-Specific Health Literacy Scale with Cronbach alpha=.71. It consists of 12 items each with 4 possible scores (1 to 4): inapplicable (1) to strongly applicable (4) where a higher score indicates a higher level of health literacy except items 1 to 4 [55]. The Iranian version of this scale was prepared after getting the developer’s permission. Thus, it was first translated into Persian by a forward-backward translation method. Then, face and content validity were approved by an expert’s opinion (nursing faculty, nurse practitioners, and cardiologists) and discussion with patients with HF. A pilot study was conducted to assess the reliability with 30 HF patients and where a Cronbach alpha value of .77 was determined. Deletion of items could not improve the value similar to the original scale. Therefore, we decided to retain all items [55]. We will ask the participants to complete the health literacy scale as a baseline survey.

In order to measure the HF knowledge at the end of the study, monthly self-care behavior, and the HFQOL, the outcome assessor will be blinded to study group assignments. The assessor will send the DHFKS, SCHFI, and MLHFQ to the participants in both groups by telegram mobile application in the morning of each monthly call follow-up and ask them to send answers before 6 pm of the same day.

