### Sample Size

In this study, the sample size was calculated based on the minimal clinically important difference (MCID) approach for self-care as measured by SCHFI for the primary outcome. No specific MCID for SCHFI was available to the best of our knowledge and based on our search of the PubMed database.

The suggested MCID for assessing dyspnea with the visual analog scale (0-100 score index) was the range 10-20 [56]. Thus, improving self-care for ≥10 scores from the baseline at the end of the study has been considered as MCID for the present study in order to reach a large sample size. According to the Jurgens et al [22] study in 2013, a mean of 70.8 for self-care in the control group at the end of study (90-days) and a fixed standard deviation of 27.2 (the largest SD) have been considered. In order to calculate sample size by G*Power free software (version 3.1.9.2), the input parameters are as following: effect size (Cohen *f*) of 0.168, the alpha error probability of .05, a statistical power of 80% to detect MCID≥10 scores between the 2 groups at the end of the study, 3 times measurement of outcome with monthly intervals, and a correlation coefficient of .5 among repeated measurements. Thus, by considering the overall attrition rates of 10%, the sample size was set at 68 participants (34 participants in each group).

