#### Secondary Analysis

Independent *t* tests between 2 groups will compare the mean of the HF knowledge score before and at the end of the study. The HFQOL at baseline and at monthly time intervals will be compared by the *P* value correction based on the multiple comparisons.

In order to describe the surveillance, the median of admissions to health care settings will be used. Also, the Kaplan-Meier survival analysis will be applied for a descriptive comparison of the surveillance and, a log-rank test will be used to detect the significance difference between the 2 groups. A hazard ratio will be reported with 95% CI.

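### The primary comparison leaves out the baseline SCHFI score that every patient provides; adjusting for it would gain precision at almost no cost, by an amount that depends on a baseline correlation the protocol does not state

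*Protocol article*

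**What the plan says.** Under Data Collection, "participants will be asked to complete baseline surveys (SCHFI, HF knowledge, HFQOL, and health literacy) by themselves in the HF clinic before randomization", so a baseline value is planned for every randomized patient.

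Under Primary Analysis, that value has one stated use: "Baseline scores for each scale of SCHFI including self-care maintenance, management, and confidence will be compared in both groups by an independent *t* test". The group comparison follows: "we will calculate the mean of monthly self-care scores in order to compare the mean of self-care behavior after the intervention in both groups". The section names no covariate for it. The regression mentioned next is meant to find factors related to self-care and is reported as odds ratios. It is not the group contrast, and it does not name baseline SCHFI.

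Under Secondary Analysis, independent t "tests between 2 groups will compare the mean of the HF knowledge score before and at the end of the study", that is, two separate comparisons with no link between them.

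Under Statistical Methods, after a Kolmogorov-Smirnov test, "A transformation approach will be used to handle non-normal distribution". No outcome is exempted.

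Under Sample Size, the target is set in SCHFI points relative to baseline: "improving self-care for ≥10 scores from the baseline at the end of the study has been considered as MCID". The planning inputs include "a fixed standard deviation of 27.2 (the largest SD) have been considered" and "a correlation coefficient of .5 among repeated measurements".

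**The concern.** A patient's self-care score before randomization is likely to predict the scores afterwards. A comparison of post-intervention means that ignores it carries that predictable variation as noise. In a trial of 68 patients, a chance difference between the arms at baseline also passes partly into the estimate. A baseline t test neither removes that difference nor detects it reliably. The target is an improvement from baseline, yet the stated comparison makes no use of baseline.

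The transformation rule raises a second, separate matter. A difference in means of transformed scores is not in SCHFI points, so it cannot be set directly against the 10-point MCID.

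**Working it through.** **Inputs (Sample Size section).** Difference 10 points; SD σ = 27.2; three outcome measurements; correlation .5 among them; alpha .05 (taken as two-sided); 68 patients, 34 per group; 10% attrition. Since 34 × 0.9 = 30.6, I use 31 per arm.

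**The plan's own figure.** With Cohen f = 0.168, three measurements and correlation .5, a repeated-measures within-between interaction test needs 60 patients (power 0.811). Then 60/0.9 = 66.7, rounded to 67 and made even at 68. The stated size reproduces, but for an interaction test. The between-groups test with the same inputs needs 188 patients before attrition. That mismatch is a separate issue; it matters here only because the power figures below start well under 80%.

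**Unadjusted comparison of three-month means.** With a common correlation r among the three follow-up scores:
- Variance = σ²(1 + 2r)/3. At r = .5 this is 0.667σ², an SD of 22.2.

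**Adjusted for baseline.** With correlation b between baseline and each follow-up score:
- Variance = σ²[(1 + 2r)/3 − b²]. At r = b = .5 this is (0.667 − 0.250)σ² = 0.417σ², an SD of 17.6.
- Ratio 0.417/0.667 = 0.625: a 37.5% cut in variance, equivalent to 1/0.625 = 1.6 times the patients. Interval width shrinks by 1 − √0.625 = 21%.

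**Power for 10 points on the three-month mean, 31 per arm, noncentral t, with follow-up correlation held at .5:**

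| Baseline-to-follow-up correlation b | Variance cut, b²/0.667 | Power | 95% CI half-width |
|---|---|---|---|
| not adjusted | – | 41% | 11.3 points |
| .3 | 13.5% | 47% | 10.5 points |
| .4 | 24% | 52% | 9.8 points |
| .5 | 37.5% | 60% | 8.9 points |

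The cut reaches one third only at b of about .47. If one common correlation is varied throughout, the cut is 17% at .3 and 61% at .7. No Bonferroni correction is applied in these figures; one would lower every power.

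**Outcomes with a single follow-up.** The variance cut is b², so 25% at .5. This applies to knowledge, which is measured at baseline and at the end only, and to a month-3 SCHFI comparison.

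**Change score.** At r = b = .5, the variance of the three-month mean minus baseline is σ²(0.667 + 1 − 1) = 0.667σ², the same as unadjusted. The gain comes from using baseline as a covariate, not from subtracting it.

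**Chance imbalance.** The baseline difference between arms of 31 has SD 27.2 × √(2/31) = 6.9 points. At b = .5, half of it passes into the unadjusted contrast, about 3.5 points.

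**Room below the ceiling.** For the planning mean of 70.8, (100 − 70.8)/27.2 = 1.07 SD at a single occasion. For the three-month mean, which is the variable to be compared, it is (100 − 70.8)/22.2 = 1.31 SD.

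**The case against.** The best defence is that the article names no test for the post-intervention comparison and does not exclude covariates. It is a condensed account, and an analysis plan not shown might add them. In part this stands: adjustment is not ruled out. But the text does fix what is compared, a post-intervention mean, and gives baseline one different use. As written, baseline is outside the group contrast.

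It is also true that the unadjusted comparison is valid. A reader might infer from the chance-imbalance figure that the planned estimate is biased. It is not: randomization makes it unbiased, and its standard error already reflects such imbalance. The loss is one of precision.

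A reader might take the loss of over a third as the plan's own figure. It is not. The .5 is given for the three monthly outcome measurements, and no correlation with baseline is stated. The article reports Cronbach alphas of .56, .64 and .79 for the three SCHFI scales. If alpha approximates reliability, which is an assumption, .5 is near the upper limit for the maintenance scale. The 37.5% is also a variance figure and does not carry over to knowledge.

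Finally, a reader might infer from the closeness of the ceiling that transformation is likely. The documents do not show this. The rule is conditional, the relevant headroom is 1.31 SD rather than 1.07, and whether the test rejects depends on details not given.

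**Conclusion.** The point holds as an avoidable loss of precision, not as an error that invalidates the analysis. The variance cut from adjustment is 13.5% to 37.5% for baseline correlations of .3 to .5, with follow-up scores correlated at .5 and an SD of 27.2. Power with 31 per arm rises from about 41% to between 47% and 60%. These powers place the 10-point difference on the three-month mean, whereas the article sets it at the end of the study.

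Adjustment does not bring the trial to 80% power and should not be presented as a remedy for the sample size. The transformation point is conditional: it matters only if the rule is applied to SCHFI, and then the contrast can no longer be read directly against the 10-point MCID.

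**What to change.** - For each SCHFI scale analysed as primary, make the group comparison an ANCOVA of the mean of months 1 to 3, or a mixed model of the monthly scores, with group and that scale's own baseline score as covariate. The article describes three separate scales and gives no single SCHFI score, so the covariate must be named scale by scale.
- Report the difference on the untransformed 0-100 scale with a robust or bootstrap 95% CI, in place of the transform-if-non-normal rule for these outcomes.
- Treat knowledge (end of study) and MLHFQ (monthly) in the same way, each with its own baseline.
- Keep baseline comparisons descriptive; do not let baseline t tests decide the analysis.

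The cost is a change of wording and one degree of freedom per ANCOVA. The baseline scores are already part of the planned data collection.

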### Study Measures

#### Primary Outcome

##### Self-Care Behavior

Effective self-care improvement is a priority of all clinicians caring for patients with HF [46]. In a developing country like Iran, there is a growing need to improve patient’s self-care [15]. However, there is a low rate of reported admissions for HF in Iran [3]. Thus, in contrast to previous studies where hospitalization was considered the primary outcome [21,22,30] and self-care as the secondary outcome [21,22], self-care has been identified as the primary outcome in this trial.

Self-care behavior will be measured by the Self-Care of Heart Failure Index (SCHFI) version 6.2 [47] by self-reporting at baseline and monthly intervals for 3 months. SCHFI was translated into Persian and validated for Persian speaking people by Siabani et al in 2014 [48]. It consists of 3 separate scales and 22 questions: 10 for self-care maintenance, 6 for self-care management, and 6 for self-care confidence [49]. Cronbach alpha was determined for self-care maintenance (.56), management (.64), and confidence scales (.79) [48]. Scale scores can range between 0 to 100, and a score ≥70 will be considered as adequate self-care [49]. We will ask participants to complete SCHFI by themselves at baseline and then monthly for 3 months.

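### No SCHFI scale is named as primary, nothing controls error across its three scales, and the sample size and the primary analysis use different endpoints

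*Protocol article*

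**What the plan says.** The protocol article deals with the primary outcome in three places.

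- **Study Measures, Self-Care Behavior.** Self-care measured by the SCHFI is primary. On the instrument: "It consists of 3 separate scales and 22 questions: 10 for self-care maintenance, 6 for self-care management, and 6 for self-care confidence". On scoring: "Scale scores can range between 0 to 100, and a score ≥70 will be considered as adequate self-care". The section gives no total or composite score and does not say which scale is the primary one.
- **Sample Size.** The calculation takes "a mean of 70.8 for self-care in the control group at the end of study" and an SD of 27.2, with alpha .05, 80% power, a 10-point difference between groups at the end of the study, three monthly measurements correlated at .5, and 10% attrition. This is one score, with its scale unnamed.
- **Primary Analysis.** The three scales are named for baseline only: "Baseline scores for each scale of SCHFI including self-care maintenance, management, and confidence will be compared in both groups". For the period after the intervention, "we will calculate the mean of monthly self-care scores in order to compare the mean of self-care behavior after the intervention in both groups", with no scale given. Then, "because of the frequent measurement of self-care behavior, we will also use" a Bonferroni P value correction. The number of tests to be corrected for is not stated.

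**The concern.** A primary outcome needs one score, one time summary and one test, or else a rule for sharing alpha among several. Here the outcome definition offers three scores, the sample size presumes one, and the analysis section does not say which. The time summary also differs: end of study in Sample Size, the average over months in Primary Analysis. The only stated multiplicity correction is justified by repeated measurement over time, so it does not address the three scales.

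At stake is whether the trial has one primary answer fixed in advance. As written, maintenance, management or confidence, at month 3 or averaged, could each be reported as the primary result, and nothing limits the chance that one of them is positive by luck.

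**Working it through.** **1. The plan's own figure.** Inputs from Sample Size: Cohen f = 0.168, m = 3 measurements, correlation .5, alpha .05, power 80%, 10% attrition. In the repeated-measures F test for the within-subject or group-by-time effect, λ = f²·N·m/(1 − ρ), with 2 and 2(N − 2) degrees of freedom. At N = 59, λ = 0.168² × 59 × 3/0.5 = 9.99 and power is 80.4%. Rounding up to 60 for equal groups and dividing by 0.9 gives 67, or 68 for equal groups. The stated 68 is reproduced as one test of one score at an undivided .05.

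The test of the group difference averaged over time has λ = f²·N·m/(1 + (m − 1)ρ). It needs N = 188 before attrition and does not reproduce 68.

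**2. The three sections side by side.**

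| | Self-Care Behavior | Sample Size | Primary Analysis |
|---|---|---|---|
| Score | three scales, no total | one, unnamed | three at baseline, unnamed afterwards |
| Time | baseline and monthly for 3 months | end of study | mean of the monthly scores |
| Alpha | – | .05, undivided | Bonferroni, for repeated measurement |

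**3. Multiplicity over time.** Averaging the monthly scores leaves one between-group comparison per scale. That comparison carries no multiplicity over months. Separate month-by-month tests would carry it, and Bonferroni is valid for those.

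**4. Multiplicity over scales.** Assume each scale's averaged score is tested at two-sided .05 and any one positive result counts as success. For independent scales, 1 − 0.95³ = 0.143. For equally correlated scales, simulation of three z tests (2 million draws) gives:

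| Correlation between scales (assumed) | Family-wise error at .05 each | At .05/3 each |
|---|---|---|
| 0 | 14.3% | 4.9% |
| .3 | 13.6% | 4.8% |
| .5 | 12.6% | 4.5% |
| .7 | 10.9% | 3.9% |
| .8 | 9.9% | 3.5% |

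Numerical integration agrees with the column at .05 to within 0.1 percentage point. The protocol gives no correlation between the scales.

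**5. Power for the endpoint that Primary Analysis uses.** The SD of the mean of three months is 27.2 × √((1 + 2 × 0.5)/3) = 22.2. With 10% attrition, 68 × 0.9 = 61.2, so about 61–62 complete.

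- 30 and 31 per arm: SE = 22.2 × √(1/30 + 1/31) = 5.69, and 10/5.69 = 1.76. Power at two-sided .05 is 41% (noncentral t).
- 31 per arm: SE = 5.64, and 10/5.64 = 1.77. Power is 43% by the normal approximation.
- For 80% power: n = 2 × (1.96 + 0.84)² × 22.2²/10² ≈ 77.4, so 78 evaluable per arm, against 34 randomized per arm.

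**The case against.** The best case for the plan has four parts.

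- **Three co-primary tests are never declared.** Primary Analysis names the scales only for the baseline comparison and then speaks of self-care as one thing, as Sample Size does. This stands. The text supports an undefined primary score. It does not support the statement that error is inflated, so the percentages above are conditional.
- **The Bonferroni sentence may be sound.** Its wording fits month-by-month tests run in addition to the averaged comparison, and Secondary Analysis plans corrected monthly comparisons for quality of life. This also stands. A reader might infer that the correction is simply misapplied, but the text does not establish that. It is redundant for the averaged comparison and valid for separate monthly tests.
- **Inflated error and lost power cannot be claimed together.** A reader might infer that the plan both inflates error across scales and loses power through a needless divisor. Those results require the same tests to be run at .05 and at .0167. If a divisor of 3 were applied to each scale's averaged test, family-wise error would be at most about 4.9%, by coincidence. The protocol states neither that divisor nor that use.
- **A condensed article may leave the testing hierarchy to an analysis plan.** That is fair for detail. It does not cover a difference in endpoint between two sections of the same article, or a primary outcome whose score cannot be identified from sections written to define, size and analyse it.

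**Conclusion.** The point holds in a limited form. No SCHFI scale is primary, nothing controls error across the three scales, and the endpoint in Sample Size (end of study) is not the one in Primary Analysis (mean of monthly scores). This is true under either reading of the Bonferroni sentence.

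The size depends on assumptions. If any one of three averaged scores tested at two-sided .05 could count as success, the chance of a false positive is 14.3% for independent scales and falls to 9.9% at a correlation of .8, which is still about twice nominal. Both the success rule and the correlations are assumed. No loss of power from the Bonferroni step is claimed.

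The low power for the averaged endpoint is not caused by the multiplicity gap. It arises because 68 reproduces as a within-subject or group-by-time test, while the planned comparison is between group means. It matters here because it limits how the endpoint mismatch can be repaired.

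**What to change.** Before unblinding:

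1. Name one SCHFI scale and one time summary, for example the month 1–3 mean, as the single primary test at two-sided .05. Make the other two scales secondary, under Holm. If all three must stay primary, apply Holm or Bonferroni across the three scales.
2. Keep any Bonferroni correction over months for supportive monthly tests only, and say so.
3. State the same scale and time summary in Sample Size, and restate the power. If the month 1–3 mean is chosen, power for 10 points is about 41–43% at .05 with 61–62 completers, SD 27.2 and correlation .5.

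Items 1 and 2 need only wording, but two scales lose primary status or share alpha. Item 3 costs more than wording: the stated power becomes less favourable, and 80% would need 78 evaluable per arm on a single scale at .05.
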